### Data collection

2.4

Assessments are conducted at the three afore mentioned time points. Evaluators have been trained in psychological evaluation. The neuropsychological assessment will be carried out in the presence of the participants. The rest of the assessment will be conducted on another day and online to increase the feasibility and prevent fatigue due to the large number of assessment instruments. The assessment of the mother and the adolescent will be conducted separately but the same evaluator. Instruments used in each evaluation and the corresponding informant (mother or adolescent) is reported in Table 1. Types and dosages of the mothers’ medication as well as attendance to psychological and/or pharmacological treatment for the adolescent children will be recorded at the three time points of assessment.

**Table 1 tab1:** Measures used in the study with mothers and their adolescent children.

Instruments	Informants		Time of assessment		
	Mothers	Adolescent	T1	T2	T3
Inclusion/exclusion criteria	X	X	X		
Informed consent	X	X	X		
Sociodemographic and clinical questionnaire	X	X	X		
Clinical symptoms			X	X	X
PANSS	X		X	X	X
CDSS	X		X	X	X
SUMD	X		X	X	X
SDQ		X	X	X	X
Metacognition and social cognition					
BCIS	X	X	X	X	X
CBQ	X	X	X	X	X
JTC	X	X	X	X	X
AIHQ	X	X	X	X	X
The Hinting Task	X	X	X	X	X
Faces Test	X	X	X	X	X
SFRT-2	X	X	X	X	X
Familiar and social functioning					
FES	X		X	X	X
GAF	X	X	X	X	X
SWLS	X		X	X	X
CGAS		X	X	X	X
SWLS-N		X	X	X	X
Protective factors					
RSES	X	X	X	X	X
CD-RISC 10	X	X	X	X	X
CSI-SF	X	X	X	X	X
SSQ	X		X	X	X
Attachment and trauma					
PAM	X		X		
MACE	X		X		
CAMI-R		X	X		
Cognitive functioning					
SCIP	X		X		X
TMT (A)	X	X	X		X
TMT (B)	X	X	X		X
WAIS IV	X	X	X		
WISC		X	X		
Matrix		X	X		X
Feasibility and acceptability^a^	X	X			X

AIHQ, The Ambiguous Intentions Hostility Questionnaire; BCIS, Beck Cognitive Insight Scale; CAMI-R, The short version of Cartes, Modèles Indivuels de Relation; CBQ, Cognitive Bias Questionnaire; CD-RISC 10, The Connor-Davidson Resilience Scale; CDSS, The Calgary Depression Scale for Schizophrenia; CGAS, Child Global Assessment Scale; CSI-SF, The Coping Strategies Inventory; CTQ-SF, Childhood Trauma Questionnaire; FES, Family Environmental Scale; GAF, The Global Assessment of Functioning; JTC, Jumping to Conclusions reasoning bias; MACE, Maltreatment and Abuse Chronology of Exposure; PAM, Psychosis Attachment Measure; PANSS, Positive and Negative Syndrome Scale; RSES, Rosenberg Self-Esteem Scale; SCIP, The Screen for Cognitive Impairment in Psychiatry; SDQ, The Strengths and Difficulties Questionnaire; SFRT-2, The Situational Feature Recognition Test 2; SSQ, Self-Stigma Questionnaire; SUMD, Scale of Unaweressness of Mental Disorder; SWLS, The Satisfaction With Life Scale; SWLS-N, Satisfaction with Life Scale for Children and Adolecents; T1, An initial no-intervention period of eleven weeks; T2, Baseline; T3, Post-intervention; TMT-A, The Trail Making Test – A; TMT-B, The Trail Making Test – B; WAIS IV, Wechsler Adults Intelligence Scale IV; WISC, Wechsler Intelligence Scale for Children. ^a^Feasibility and Acceptability will be assessed in all sessions of the MCT-F by both participants.

### Interventions

2.5

The intervention consists of an adaptation of classical MCT to a family setting (MCT-F), that is, for mothers with psychosis and their adolescent children in a group setting with other peers. Metacognitive training for psychosis is a psychological intervention that combines psychoeducation with a cognitive behavioral intervention in a metacognitive approach (Moritz and Woodward, 2007). It consists of a normalizing approach to work on cognitive biases which present in the general population but that are more prevalent in people with psychosis, as they are involved in the appearance and maintenance of delusions (Freeman, 2007; Moritz and Woodward, 2007).

Before the quasi-experimental study, a first stage consisted of adapting MCT to this population using the first six steps of the ADAPT-ITT method through a participatory approach, which included the first-person perspective and involved qualitative and quantitative methods. While the core components of the original MCT intervention were retained, patients, relatives, adolescents, and experts participated to ensure that MCT-F was appropriate and acceptable (Espinosa et al., 2024).

The final version of MCT-F consists of 11 online weekly group sessions lasting 60 min. The groups will be composed of 3–4 mothers with psychosis, their adolescent children and two therapists. This group size is large enough to allow for some participants’ absence from sessions without leaving those attending feeling exposed. It is also manageable for two facilitators. Furthermore, participants will be allocated to their groups based on the teenagers’ ages (aged 12–16 and 16–20) to adapt examples and vocabulary and so they feel more comfortable sharing experiences. Mothers and adolescents will be able to attend sessions from the same room or from separate places, to facilitate attendance and the intimacy of both participating groups. Therapists will also be local community references to the participating mothers to enhance adherence and assure the inclusion of the study’s information in their clinical records. Although there is no minimum number of group sessions that participants must attend, the attendance of each participant will be recorded.

The material available to use during MCT-F is made up of power-point presentations. Each module contains therapeutic material including psychoeducational information, exercises, case examples and demonstrations. The first session is added as a psychoeducation session to explain the psychotic illness, metacognition, and training objectives. Seven of the therapeutic modules address cognitive bias and errors that are frequently seen in problem-solving in psychosis. The other two modules work with depression, self-esteem, and self-stigma. Lastly, we added an additional session, after third session, with mothers and adolescent children attending separately to facilitate speaking openly about feelings or concerns without their relatives.

All mother participants will also receive their treatment as usual (TAU). In order to account for differences in TAU over the different centers the mothers participate in, we will collect the specific treatment characteristics of the TAU offered in each institution.

### Sample size calculation

2.6

Taking as a reference previous data on effectiveness of MCT in women samples (Salas-Sender et al., 2020), the sample size necessary for the study to have adequate power has been estimated. With an alpha of 0.05, a power of 0.90, a difference between pre-treatment and post-treatment in cognitive insight (self-certainty) of 2 points in the intervention vs. −0.48 in the control, and with a SD of 4.14 in the reference group, as well as considering possible losses of 25%, the final sample calculation is estimated to be of 48 mothers (with their respective children) in total.

### Data analysis

2.7

The main analysis variable will involve the difference between scores in the control assessment and intervention assessment for the cognitive insight assessed in the mothers with psychosis. Secondary outcomes will be the changes in other assessments of metacognition and social cognition variables, familiar and social functioning, cognitive distortions, cognitive functioning, protective factors, and self-stigma.

The changes in the cognitive insight scales’ scores will be analyzed using repeated measures regression methods. Changes in the scores of symptoms, metacognition and social cognition, social functioning, understanding of the disease, self-esteem, resilience and coping strategies in adolescent children will be analyzed using repeated measures regression methods, with the final score of the scale as the dependent variable. Two additional analyses will be carried out to examine the robustness of the results. First, the intention-to-treat analysis will be performed after replacing missing values for the dropout cases using the method “last observation carried forward” (LOCF). Next, the analyses will be performed only with data from participants who complete the treatment and who have been evaluated at both time points. Finally, the satisfaction of patients undergoing group treatment will also be analyzed.

All the analyses will be controlled by medication changes, cognitive functioning, attachment, trauma, start of the illness before motherhood and type of TAU (in mothers), and the presence of mental disorders or attendance to psychological and/or pharmacological treatment (in adolescents).

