**Materials and methods:**

A quasi-experimental design with participants acting as their own control will be carried out. Forty-eight mothers with psychosis and their adolescent children (between 12 and 20 years old) recruited from a total of 11 adult mental health care centers will receive MCT-F. Participants will be evaluated 11 weeks before the intervention (T1), at baseline (T2), and post-intervention (T3) with a cognitive insight scale, as a primary outcome. Measures of metacognitive and social cognition, symptoms, cognitive functioning, family and social functioning, protective factors (self-esteem, resilience, and coping strategies) and self-perceived stigma will be addressed as secondary outcomes. Assessment will also address trauma and attachment in mothers and, lastly, the feasibility and acceptability of MCT-F in both participant groups.

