### Study aims

1.5

The objective of this study is to evaluate the efficacy of Family Metacognitive Training (MCT-F) in mothers with psychosis and adolescent children in an online group setting to improve family relationships, cognitive insight, symptoms of women with psychosis, and increase their children’s knowledge of the disease. As secondary objectives, we aim to evaluate improvements in metacognition and social cognition, symptoms, protective factors and self-perception of stigma. Finally, we aim to evaluate the feasibility and acceptability of MCT-F in both mothers with psychosis and their adolescent children.

We expect that MCT-F will be effective to improve cognitive insight in mother with psychosis as first hypothesis. As a secondary hypothesis we expect that MCT-F will improvement familiar functioning, metacognition and social cognition variables, as attributional style and Theory of mind, protective factors such as self-esteem, resilience and coping strategies and will decrease self-stigma in mothers. Regarding adolescent children’s participants, we hypothesize that MCT-F will increase children’s knowledge of their mothers’ disease and help them to better understand their mother’s thoughts and their understanding of metacognition and, consequently, to decrease anxiety and depressive symptoms. Furthermore, we expect an improvement in familiar functioning, metacognition and social cognition variables, as well as in protective factors such as: self-esteem, resilience, and coping strategies. More precisely, we expect that all outcomes’ measures will significantly improve from pre- to post-assessment and significant differences when compare with control evaluation. We will control the analysis by cognition functioning, previous trauma and attachment of the mother, presence of the illness before motherhood and attachment of the adolescent with their mother. Finally, we expected that MCT-F Twill be feasible and acceptable to both mothers and their adolescent children.

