### Study design and procedure

2.1

The study follows a quasi-experimental design with participants acting as their own control. It was approved by the ethic committees of each participating center and by the Research and Ethics Committee of Parc Sanitari Sant Joan de Déu (PSSJD) (coordinating center) and it conforms to the declaration of Helsinki. All participants meeting the inclusion criteria will receive MCT-F. We will conduct three assessments separated by 11 weeks: an initial no-intervention period of eleven weeks (T1), baseline (T2); and post-intervention (T3).

A complete flowchart of the study can be found in Figure 1. All potentially eligible study participants are recruited from March 2024 to May 2024 by their referring mental health professional from the following 11 participating centers of outpatient mental health services: Hospital de la Santa Creu y Sant Pau (Barcelona), Fundación Jiménez Diaz (Madrid), Corporació Sanitària i Universitària Parc Taulí (Sabadell, Barcelona), Centre d’Higiene Mental de Les Corts (Barcelona), Institut Pere Mata (Reus, Tarragona), Hospital Marqués de Valdecillas (Santander), Parc Salut Mar (Barcelona), Hospital de Mataró (Mataró, Barcelona), Fundació Vidal i Barraquer (Barcelona), Hospital Virgen del Rocío (Sevilla), Mutua de Terrassa (Terrasa, Barcelona), and the coordinating center Parc Sanitari Sant Joan de Déu (Sant Boi, Barcelona). All selected mothers are informed of the study objectives and methodology by their referring mental health professional and sign the required informed consent form. In the case of adolescent participants under the age of 18, in addition to their own consent, the consent of their parents, guardians, or legal representatives is obtained. Then, a psychologist from the research team contacts participating mother by telephone to confirm if she and her adolescent child/children accomplish inclusion criteria. After confirmation of their eligibility, they are enrolled in the study. Specific schedules for the administration of the instruments and the data collection procedure are described below.

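### Cognitive functioning is listed as a secondary change outcome, but none of its tests is scheduled at T2, so no own-control comparison can be formed for it

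*Protocol article*

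**What the plan says.** **Outcome status.** The abstract (Materials and methods) names the secondary outcomes in a list that opens with "Measures of metacognitive and social cognition, symptoms, cognitive functioning, family and social functioning". Section 2.7 repeats this and says that secondary outcomes are analysed as changes, again naming "familiar and social functioning, cognitive distortions, cognitive functioning, protective factors, and self-stigma". Metacognition, social cognition and cognitive distortions appear separately in that sentence, so cognitive functioning must mean the Table 1 block headed "Cognitive functioning": SCIP, TMT, WAIS, WISC and Matrix.

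**Comparison.** Section 1.5 states the expectation that "all outcomes’ measures will significantly improve from pre- to post-assessment and significant differences when compare with control evaluation". Section 2.1 supplies the control by describing a "quasi-experimental design with participants acting as their own control". Visits are 11 weeks apart: T1 opens the untreated period, T2 is baseline and T3 follows the intervention.

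**Schedule.** In Table 1 (section 2.4), SCIP, TMT-A, TMT-B and Matrix are marked at T1 and T3, with the T2 cell empty. WAIS and WISC are marked at T1 only. The instruments for symptoms, metacognition and social cognition, functioning, protective factors and self-stigma are marked at all three visits.

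**Covariate role.** Sections 1.5 and 2.7 also use cognitive functioning as an adjustment variable.

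**The concern.** The study has no separate comparison group. What it offers instead is that each participant's change over the untreated 11 weeks serves as the reference for her change over the treated 11 weeks. That needs a measurement at T2, where one period ends and the other begins. For cognitive functioning there is none.

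The tests concerned are performance tests, and the TMT score is a completion time (section 2.3.1.6). Improvement through familiarity with the test is therefore a plausible rival explanation for any gain. Medication change and the passage of time are others. The limitations paragraph of the Discussion concedes that isolating the effect of MCT-F may be difficult. It relies on the own-control design, together with the planned analyses, to meet that difficulty. For this one secondary domain the design part of that safeguard is missing, so a gain from T1 to T3 could be read as a treatment effect without any control information behind it.

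**Working it through.** The protocol states no figure for this point, so there is none to reproduce. The check sets the comparison in sections 1.5 and 2.1 against the visits in Table 1.

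**Step 1: the contrasts the design needs.**

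- Control-period change: C = T2 − T1 (11 weeks, untreated)
- Intervention-period change: I = T3 − T2 (11 weeks, treated)
- Own-control comparison: I − C = (T3 − T2) − (T2 − T1) = T3 − 2·T2 + T1

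T2 enters the comparison with weight −2, so it cannot be recovered from T1 and T3 alone.

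**Step 2: what Table 1 allows.**

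| Instrument | Visits marked | T2−T1 | T3−T2 | T3−T1 |
|---|---|---|---|---|
| SCIP (mothers) | T1, T3 | no | no | yes |
| TMT-A (both) | T1, T3 | no | no | yes |
| TMT-B (both) | T1, T3 | no | no | yes |
| Matrix (adolescents) | T1, T3 | no | no | yes |
| WAIS | T1 | no | no | no |
| WISC | T1 | no | no | no |
| BCIS, for comparison | T1, T2, T3 | yes | yes | yes |

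No cognitive test yields a control-period change or an intervention-period change. WAIS and WISC yield no change at all.

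**Step 3: what T3−T1 contains.** By identity, T3 − T1 = (T2 − T1) + (T3 − T2) = C + I. It covers 11 + 11 = 22 weeks, of which 11/22, or half, are untreated. It is also the first repetition of the test, so any retest gain lies wholly inside it. It is one observed quantity for two unknowns. Every participant follows the same sequence, so no regression model can separate C from I with these data.

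**Step 4: could the missing-data rule fill the gap?** No. Section 2.7 applies last observation carried forward to dropouts, and a visit at which a test was never planned is not a dropout. If T1 were nevertheless carried to T2, C would be zero by construction and all of T3−T1 would be credited to the intervention.

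**The case against.** The strongest case on the other side has five parts.

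**The control comparison is not clearly meant for this domain.** Section 2.7 attaches the control-versus-intervention difference to the mothers' cognitive insight and describes the secondary outcomes only as changes. The specific hypotheses in section 1.5 and in the Discussion do not name cognitive functioning, and section 1.5 goes on to name it as a control variable. This makes the point smaller, since no named hypothesis depends on it. It does not remove it: the general sentence in section 1.5 covers all outcome measures, and the abstract and section 2.7 both list cognitive functioning as an outcome.

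**The table may be at fault.** Table 1 has other flaws. FES is not marked for adolescents although section 2.3.2.3 says they receive it, and the legend defines an abbreviation that no row uses. The sponsor should confirm the schedule. Still, the blank T2 cell is the same in four rows, which looks deliberate.

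**Leaving out T2 may be sensible.** It spares participants an in-person session and one exposure to the tests. That is a fair reason for the schedule, but a measure scheduled this way cannot also be a controlled outcome.

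**Dual use is not an error.** A reader might infer that listing the same variable as outcome and covariate is a second defect. The document does not support that. T1 values can serve the adjustment, and adjusting for the baseline of a variable that is also followed up is ordinary practice.

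**The harm is not written into the plan.** A reader might infer that the trial will report T3−T1 as the effect of MCT-F, or might attach a size to the bias in standard deviations. The protocol nowhere says that T3−T1 will be the pre-post effect; it calls T2 the baseline. Nor does it give any retest gain for these tests, so a figure for the bias would only return whatever gain was assumed.

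**Conclusion.** The point stands as a conflict between the outcome list and the assessment schedule. As printed, the own-control comparison expected of all outcome measures cannot be delivered for cognitive functioning, in mothers or in adolescents. The only change available is T3−T1 on SCIP, TMT-A, TMT-B and Matrix. It spans 22 weeks, half of them untreated, and cannot be attributed to MCT-F. The size and direction of the resulting bias cannot be derived from the document.

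The conclusion assumes that Table 1 shows the intended schedule and that the general expectation in section 1.5 applies to every outcome listed in section 2.7. It concerns one secondary domain only. The primary outcome is not touched, because BCIS is measured at T1, T2 and T3 and both periods can be compared.

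**What to change.** First confirm that the blank T2 cells in Table 1 are intended. If they are:

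- In the abstract, section 1.5 and section 2.7, exempt cognitive functioning from the controlled efficacy comparison.
- State in section 2.7 that T3−T1 on SCIP, TMT-A, TMT-B and Matrix will be reported as a descriptive, uncontrolled 22-week change, with no efficacy claim.
- State that the T1 values are the ones used for the adjustment already planned in sections 1.5 and 2.7. That adjustment should be kept.
- Date and justify the change of outcome status. Section 2.1 gives recruitment as March to May 2024, so the change should not appear as a silent edit.

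The cost is one secondary efficacy claim. The rest is wording and a dated record; no visit, instrument or sample size changes.

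The alternative is to test at T2 as well, which would make both period changes computable. It costs an added in-person session, since section 2.4 has the neuropsychological tests done face to face. It also leaves practice effects in both periods: T2−T1 would hold the first retest gain and T3−T2 the second. If gains shrink with repetition, the comparison would be biased against MCT-F. For these reasons the descriptive report is the better choice here.

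### The only analysis labelled intention-to-treat fills dropouts by last observation carried forward, which distorts the own-control contrast even under random loss; the completer set is undefined

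*Protocol article*

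**What the plan says.** Section 2.7 (Data analysis) names repeated measures regression for the change in cognitive insight and then adds two analyses meant to test robustness.

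- **Intention-to-treat.** "the intention-to-treat analysis will be performed after replacing missing values for the dropout cases using the method" LOCF. No other analysis in the article carries the intention-to-treat label.
- **Completers.** Limited to participants "who complete the treatment and who have been evaluated at both time points".

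Two other sections bear on these rules. Section 2.1 states "We will conduct three assessments separated by 11 weeks": T1, then T2 as baseline after a no-intervention period, then T3 after the intervention. Section 2.5 says "there is no minimum number of group sessions that participants must attend", with attendance recorded.

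Section 2.6 supplies the planning figures: a change "of 2 points in the intervention vs. −0.48 in the control", "with a SD of 4.14 in the reference group", and "as well as considering possible losses of 25" per cent.

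**The concern.** The study has no comparison group. Its only control is each mother's change over the waiting period, so the effect is a difference between two changes and uses all three visits. In a two-arm trial, carrying a value forward sets one change to zero. Here the T2 value enters the contrast twice, once as the end of the control period and once as the start of the intervention period. Filling T3 from T2 therefore removes the intervention change but keeps the control change with its sign reversed.

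The plan expects a quarter of the mothers to be lost, so this affects a sizeable share of the intention-to-treat result. If that result is then compared with the main model to judge robustness, agreement or disagreement may reflect the filling rule rather than the intervention. The completer analysis does not offer a clear second check, because a reader cannot tell from the text who belongs in it.

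**Working it through.** **Inputs.** From section 2.6: intervention-period change i = +2, control-period change c = −0.48, loss 25%, SD 4.14, N = 48. From section 2.1: three visits. Section 2.7 does not write the contrast as a formula. I read it as (T3−T2)−(T2−T1), which fits the two changes used for the sample size. The plan gives no figure for the effect of LOCF, so there is none to reproduce. The planned contrast is i − c = 2 − (−0.48) = 2.48.

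**What LOCF does to one mother**

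- Seen at all visits: expected contrast i − c = 2.48.
- Lost after T2 (T3 := T2): 0 − c = +0.48.
- Lost before T2 (T2 and T3 := T1): 0 − 0 = 0.

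**Completely random loss.** Expected LOCF contrast = p(complete)·(i − c) + p(lost after T2)·(−c) + p(lost before T2)·0.

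- All losses after T2: 0.75 × 2.48 + 0.25 × 0.48 = 1.86 + 0.12 = 1.98.
- Split evenly: 1.86 + 0.125 × 0.48 = 1.92.
- All losses before T2: 1.86.

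The shift is −0.50 to −0.62 points. As a share of the planned effect, 0.50/2.48 = 20% and 0.62/2.48 = 25%.

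**No effect, steady trend (true contrast 0), random loss after T2.** With −0.48 per period: 0.25 × 0.48 = +0.12. With an assumed +1 per period: 0.25 × (−1) = −0.25. The sign follows the trend.

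**Non-random loss, by simulation.** Trials of 48 mothers, normal scores with SD 4.14, correlation between visits assumed to be 0.5 or 0.7, about 25 to 27% lost after T2, 2,500 to 6,000 runs per scenario. The plan gives neither the correlation nor the dropout mechanism, so these figures show direction and rough size only.

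| Loss mechanism | True | LOCF | Completers (all three visits) | Likelihood, all observed visits |
|---|---|---|---|---|
| Random | 2.48 | 1.97 to 1.99 | 2.46 to 2.49 | not tabulated |
| Low T2 score | 2.48 | 1.57 to 1.73 | 1.44 to 1.91 | 2.47 to 2.51 |
| Poor response | 2.48 | 2.56 to 2.76 | 3.83 | 2.95 to 3.26 |
| Poor response, no effect | 0 | about 0.6 to 0.9 | 1.36 | 0.61 to 0.78 |

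In the last row, the LOCF type I error was about 0.11 with no change in either period and about 0.13 with a steady −0.48. With a steady +1 per period the LOCF value was smaller, +0.41. Coverage of the true 2.48 by the LOCF 95% interval was 89 to 91% under random loss and 82 to 85% when loss followed the T2 score.

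**Completer set.** Section 2.1 has three assessments, while section 2.7 asks for two and does not name them. Section 2.7 requires completion of treatment, while section 2.5 sets no attendance threshold that would define it. Two analysts could build different sets from this text.

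**The case against.** **These are additional analyses.** This stands. Section 2.7 presents both as robustness checks, and nothing says that the main regression uses LOCF. Its handling of missing data may be in an analysis plan that is not shown, and it may already be the likelihood model proposed here. This limits the point to what the plan calls intention-to-treat and to what its robustness checks can show.

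**A diluted estimate is proper for intention-to-treat.** Only in part. If a lost mother is taken to have had no benefit, her contrast is 0 and the average is 0.75 × 2.48 = 1.86. LOCF gives 1.98 when losses fall after T2, because it credits each such mother with +0.48. It does not implement that assumption consistently either.

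**Likelihood is not a cure.** This stands. It recovers 2.5 only when loss depends on observed values. When poor responders left, LOCF (2.56 to 2.76) was nearer to 2.48 than likelihood (2.95 to 3.26), and under no effect both were biased upward.

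Three stronger readings are tempting but not supported:

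- *Both checks are biased because of the two-visit wording.* Completers are unbiased under random loss. Their bias in the other scenarios is selection, and it arose with all three visits present.
- *The completer analysis drops the control period.* The two visits are not named. Table 1 places eligibility and consent at T1, so a mother seen at T2 and T3 would normally have T1. Section 1.5 also states a separate pre-to-post expectation, for which two visits would be natural.
- *The LOCF interval is too narrow because filled values count as real.* In simulation its standard error matched its own sampling SD (0.945 against 0.952 to 0.960 at correlation 0.5). The poor coverage of 2.48 comes from bias.

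**Conclusion.** The point holds for the LOCF rule. On the plan's own inputs, and with no assumption beyond random loss and the three-visit reading of the contrast, the analysis labelled intention-to-treat understates the planned effect by 20 to 25% (1.86 to 1.98 against 2.48). Under other loss patterns it moves down or up. Those sizes rest on assumed correlations and dropout mechanisms; the lack of a fixed direction does not depend on the exact values. LOCF is neither unbiased nor reliably conservative, so it cannot test the robustness of the main result.

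The completer point is smaller: the set is undefined, and no bias from its wording has been shown. The main analysis is not shown to be affected by either rule.

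**What to change.** In section 2.7, or in the analysis plan before the data are analysed:

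1. Define the intention-to-treat analysis as the repeated measures regression already named, fitted by likelihood with an unstructured covariance to all observed T1, T2 and T3 values of every enrolled mother.
2. Remove LOCF as the intention-to-treat rule.
3. Use a delta-adjusted (missing-not-at-random) analysis as the sensitivity check, for instance by multiple imputation, because the likelihood model is also biased when loss depends on unobserved response.
4. State the completer set as mothers measured at T1, T2 and T3, and report attendance separately.

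The cost is wording and a little more analysis work; no data collection changes. The interval will be wider, because mothers lost to follow-up no longer count as observed with no change: under random loss at correlation 0.5 the LOCF standard error was 0.95, against 1.19 for completers. That width is the more honest statement of what the data show about the contrast.
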